### Study outcomes

#### Primary outcome

The primary outcome in this study is a summary composite metric of poor childbirth outcomes. The component outcomes of the summary outcome are those anticipated to be preventable by the correct utilization of the modified WHO-SCC. They will encompass in this study: stillbirths, maternal deaths, early neonatal deaths, severe postpartum hemorrhage, maternal infections, early neonatal infections, prolonged obstructed labor, severe pre-eclampsia, uterine rupture in the health facility, eclampsia and maternal near miss. The definitions for the above severe complications are based on WHO clinical and laboratory-based criteria [22].

The presence/absence of each of the above poor childbirth outcomes will be ascertained in each birth event using data extraction from registries and patients’ charts. Different data sources will be used to cross-validate the information. These include birth registries, partograph, temperature sheet and mothers’ health books.

Regarding all these items the standards in all countries are anticipated to be similar. Other secondary outcomes that will be analyzed separately include the use of transfusion services and the return within 7 days to the health facility after discharge for complications related to the mother or the new-born. Two waves of supplies ‘availability assessments (initial assessment prior to the launch of the intervention and final assessment at the end of the study) will be conducted in both intervention and control health facilities.

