### Data collection and follow up procedures

Two data collection techniques will be used: a direct observation of healthcare providers’ performance of best practices and data extraction from various source documents to assess childbirth outcomes.

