Two data collectors will be appointed permanently (day and night) in each regional hospital during the period of data collection to directly observe and document the healthcare providers’ practices. The observations for each birth event will take place at four critical junctures from admission to discharge: at the admission, before the woman starts pushing, soon after delivery and just before discharge from the hospital. The observation will be strictly passive with no interaction with the healthcare providers and the patients. However, the data collectors can alert the healthcare providers in the event of occurrence of a life-threatening complication. Furthermore, should healthcare providers not adhere to a standard putting mother-new-born pair at high risk (examples: no administration of ARTs, antibiotics, sulfate of magnesium when needed), the observer will intervene in a kindly manner to suggest that such practice may be worthwhile. The intervention of the observer will follow a suggestive process without any coercion on the healthcare provider being observed. In such a case it will be recommended to probe the healthcare provider questioning the relevance of such a practice. For example, what do you think of the administration of ARTs to this woman? Would that be relevant? The healthcare provider must not be driven to feel guilty or blamed for anything. Any suggestion deemed relevant will be made in an inconspicuous manner, meant to be a private communication between the observer and the relevant healthcare provider. If an EBP was adhered to only after a suggestion was made by the data collector, her/she will still record that particular EBP as not having been adhered to by the healthcare provider.

The observation will be conducted every day of the week and at any time without discontinuation until the target sample size is achieved. A data collector may observe only part of a birth event and the observation will be continued by another data collector. However, data on each critical juncture must be fully collected by the same data collector. Thus, once a data collector has initiated the observation for a given pause points, he/she can get off work only after having filled in all the items pertaining to that pause point.

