#### Data extraction

The data extraction will be carried out using a standardized questionnaire performed into electronic devices. Using different sources of information including a modified birth registry, patients charts and maternal health books where available, we will collect socio-demographic and childbirth outcomes data in both control and intervention health facilities on all consecutive eligible women that were admitted for labour and delivery from 2 weeks after the launch of the intervention to 8 months. The data extraction in each health facility will be conducted twice-weekly by facility-based trained coaches. They will review data source documents to collect information on each eligible mother-new-born pair from admission to 7 days after delivery. Based on the calculated sample size, we will need to include and extract data on 320 childbirth events in each health facility. Based on the minimum average of two childbirths events per 24 h, each health facility is expected to have cared for at least 320 pregnant women in 6 months from the launch of the study.

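### The primary composite nominally runs to day 7 but is read passively from facility records and any available health books, so events after discharge are only partly observed

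*Protocol article*

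**What the plan says.** Under Data extraction, facility-based coaches work twice a week in every hospital, and the window is set there: "They will review data source documents to collect information on each eligible mother-new-born pair from admission to 7 days after delivery". The Primary outcome section says that the presence or absence of each component "will be ascertained in each birth event using data extraction from registries and patients’ charts". On the sources used for cross-checking it says: "These include birth registries, partograph, temperature sheet and mothers’ health books". The extraction section gives a similar list: "Using different sources of information including a modified birth registry, patients charts and maternal health books where available".

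The section on data collection and follow-up opens with a count of methods: "Two data collection techniques will be used: a direct observation of healthcare providers’ performance of best practices and data extraction from various source documents". Under Direct observations, the last of the four observed junctures is "just before discharge from the hospital", so observation ends when the family leaves. No home visit, telephone call or other contact after discharge is described.

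The composite includes maternal deaths, early neonatal deaths, maternal infections and early neonatal infections. All four can occur after discharge and within 7 days of birth. The Primary outcome section also lists, among other secondary outcomes to be analysed separately, transfusion use and, next to it, "the return within 7 days to the health facility after discharge for complications related to the mother or the new-born".

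**The concern.** The window and the sources do not match. Up to discharge, both arms are under the hospital's eye. From discharge to day 7, the plan relies on paper that reaches the hospital. A newborn who dies at home on day 4 and is never reported back is coded as having no event. So is a mother treated elsewhere for infection whose health book is not seen again. The same event in a family that comes back is coded as present.

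Two things are at stake. First, a claim about 7-day outcomes would rest on incomplete observation of exactly those components that can occur after discharge. Second, the intervention acts at four junctures, and the observed junctures place the last one just before discharge. If that step alters how long families stay or whether they return, it alters the chance that a later event is recorded. That would be a difference in detection between the arms, which a larger sample does not remove.

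**Working it through.** **The passages side by side**

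| Element | Where | What it fixes |
|---|---|---|
| Window | Data extraction | Admission to 7 days after delivery |
| Sources | Primary outcome; Data extraction | Registries, charts, partograph, temperature sheet, health books where available |
| Techniques | Data collection and follow up procedures | Two: direct observation and document extraction |
| End of direct observation | Direct observations | Discharge |

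After discharge only document extraction remains. An event is counted only if it reaches the facility's papers or a health book that is presented there.

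**The plan's own figure**

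Inputs from the Sample size section: 15% in control, halved to 7.5%; two-sided 5%; 80% power; ICC 0.01; cluster size 300; 5% non-response.

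- Two proportions, pooled variance, no continuity correction: 278 per arm.
- Design effect: 1 + (300 − 1) × 0.01 = 3.99.
- 278 × 3.99 = 1109 per arm; 1109 / 300 = 3.70, rounded up to 4 clusters = 1200 per arm.
- 2400 / 0.95 = 2527, against the stated 2530.

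The sample size reproduces, so no figure in the plan is disputed. On the same simple basis, 1200 / 3.99 = 301 effective births per arm give 83.1% power for 15% against 7.5%.

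**Effect of partial capture (assumptions, for illustration)**

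Let *s* be the share of events that arise only after discharge and *c* the chance that such an event reaches the records. Neither is in the documents. The observed rate is *p* × (1 − *s* + *s* × *c*).

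Worked case, *s* = 20%, capture 30% in control and 60% in intervention, true halving:

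- Control: 0.15 × (0.80 + 0.20 × 0.30) = 0.15 × 0.86 = 12.9%.
- Intervention: 0.075 × (0.80 + 0.20 × 0.60) = 0.075 × 0.92 = 6.9%.
- Observed risk ratio: 6.9 / 12.9 = 0.535.

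Reversed (60% control, 30% intervention): 0.15 × 0.92 = 13.8%; 0.075 × 0.86 = 6.45%; ratio 0.467.

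| *s* | Equal capture 30%: RR, power | 30% control / 60% intervention: RR, power | 60% control / 30% intervention: RR |
|---|---|---|---|
| 10% | 0.50, 80.0% | 0.516, 76.9% | 0.484 |
| 20% | 0.50, 76.4% | 0.535, 69.4% | 0.467 |
| 30% | 0.50, 72.5% | 0.557, 60.5% | 0.449 |

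With no true effect, the ratio is (1 − *s* + *s* × *c*) in intervention over the same term in control. For 30% control and 60% intervention it is 0.96/0.93 = 1.03, 0.92/0.86 = 1.07 and 0.88/0.79 = 1.11 for *s* = 10%, 20% and 30%. Reversed, it is 0.97, 0.93 and 0.90.

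**In percentage points**

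Suppose 2% to 4% of control births have their first component event after discharge, and capture is 30% in control against 40% to 60% in intervention.

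- Post-discharge events equally frequent in both arms: 0.02 × 0.10 = 0.2 points, up to 0.04 × 0.30 = 1.2 points.
- Post-discharge events also halved, which is the case consistent with the planned 7.5-point difference: 0.01 × 0.10 = 0.1 points, up to 0.02 × 0.30 = 0.6 points. That is 0.1 / 7.5 = 1% to 0.6 / 7.5 = 8% of the planned difference.

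Lower capture in the intervention arm would give an artefact of the opposite sign.

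**The case against.** The strongest reply has four parts.

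1. **This is a condensed article.** The extraction section introduces its sources with *including* and mentions a modified registry whose content is not shown. The Quality control section refers to a manual with detailed procedures. Day-7 status might be obtained in ways not printed. This stands in part: it is wrong to say that only hospital documents are used, since health books are listed. But the article states the window, names the sources and counts two techniques. The point is that stated combination and not a missing detail.

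2. **The bias mechanism is inferred.** The items at the discharge step are not given. Of the anticipated practices under Secondary outcomes, family planning is the only clear pre-discharge topic. A reader might conclude that the checklist will bring more families back and so look worse on the composite. The documents do not support a direction. This objection stands, and the point claims only that capture could differ, either way.

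3. **Return within 7 days is not misclassified.** A reader might infer that the plan treats return as a poor outcome and so penalises good discharge advice. It does not. Return sits outside the composite, beside transfusion use, among outcomes analysed separately. No reclassification is needed.

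4. **Ending the primary outcome at discharge would not cure the problem.** Observation time would then equal length of stay for every birth, and a longer stay in one arm would raise its count. This stands, so truncation belongs in a sensitivity analysis and not in the primary definition.

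In addition, stillbirth, obstructed labour and uterine rupture in the facility are unaffected. The 15% rate comes from health-system data and may already reflect record-based capture, in which case the power loss under equal capture is overstated.

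**Conclusion.** The point holds in a limited form. As written, the primary composite has a 7-day window that its sources cover fully only to discharge, so maternal and early neonatal deaths and infections after discharge are partly observed. With equal capture, the risk ratio is roughly unchanged. In the illustration, power falls from 83.1% to between 80.0% and 72.5%. With unequal capture of 30% and 60%, a true risk ratio of 0.50 would be seen as anything from 0.449 to 0.557, depending on which arm is captured better and on how many events arise after discharge.

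All capture rates and post-discharge shares are assumptions, and the power figures use the plan's own design effect without allowing for the small number of pairs. The documents establish neither that capture will differ by arm nor in which direction. What they do establish is that the trial, as described, could not tell a detection difference from a real one after discharge, and that complete 7-day outcomes cannot be claimed.

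**What to change.** Keep the day-7 composite as primary, and make its limits visible:

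- Add the discharge date and the date of each component event to the extraction form, in both arms.
- Report the composite split into events before discharge and events from discharge to day 7. Label the latter *events known to the delivering hospital*.
- Prespecify the in-hospital composite (admission to discharge) as a sensitivity analysis, and read it together with length of stay by arm.
- Report return within 7 days by arm alongside it, leaving its status as a separate secondary outcome as it is.
- Word the conclusion as facility-recorded events up to day 7 and not as complete 7-day outcomes.

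The cost is a few date fields and one extra analysis, with no new staff. These changes expose a detection artefact but do not recover the missed events. Identical day-7 contact in both arms would recover more of them, at the higher cost of a new data collection step.

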#### The incidence of poor childbirth outcomes

The component outcomes of the summary primary outcome are relatively infrequent events. Looking at recent health system information data from the three countries, we estimated that at least one of the component outcomes would be observed in an average 15% of vaginal deliveries in the study settings. With a bilateral type I error set at 5%, and a half reduction in the incidence of the primary outcome for the intervention group considered sufficient to prove the effectiveness of the intervention, we would need to observe a minimum of 1200 childbirths in each group (4 clusters per group) for a statistical power of 80%, assuming an intra-class correlation coefficient of 0.01 [23] and an average cluster size of 300. The calculated sample size was adjusted for a non-response rate of 5%. The final required sample size per country is therefore of 2530 childbirth events, half in each trial arm.

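### Returns are defined over 7 days from discharge, but data collection ends 7 days from delivery, so every day between delivery and discharge removes one day of the outcome window

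*Protocol article*

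**What the plan says.** The Primary outcome section of the protocol article, after describing the composite, names further secondary outcomes to be analysed separately. One of them is "the return within 7 days to the health facility after discharge for complications related to the mother or the new-born". Its clock starts at discharge.

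The Data extraction section is the only place that describes how childbirth outcomes are collected over time. On frequency it says: "The data extraction in each health facility will be conducted twice-weekly by facility-based trained coaches". On the period covered for each pair it says: "They will review data source documents to collect information on each eligible mother-new-born pair from admission to 7 days after delivery". That clock is tied to delivery.

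The Direct observations section treats delivery and discharge as different moments; the last two of its four observation points are "soon after delivery and just before discharge from the hospital".

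No section describes contact, record review or follow-up of a pair beyond day 7 after delivery. The 6-month limit (Study participants and recruitment) and the 8-month limit (Data extraction) govern which admissions are included, not how long each pair is followed.

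**The concern.** The outcome definition and the collection rule agree only for a pair discharged on the day of birth. For every other pair, the final part of the defined window falls after collection has ended.

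Two things are at stake. First, returns in the uncovered days are not captured, so the outcome is undercounted against its own definition. Second, the covered time depends on how long the pair stays after delivery. Stay is determined after randomisation, and the intervention could influence it: it aims to prevent complications, and one of the checklist's junctures concerns discharge. The Statistical methods section compares secondary outcome rates between arms. If stay differed by arm, the arms would be compared over unequal observed time. Analysis cannot recover returns that were never extracted.

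**Working it through.** **Inputs**
- Outcome window: 7 days, starting at discharge (Primary outcome section).
- Collection ends: day 7 after delivery (Data extraction section).
- L = days from delivery to discharge. The article gives no value, so a range is assumed. Time from admission to delivery does not enter, because both clocks start at delivery or later.

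**Formulas**
- The outcome window runs from day L to day L + 7 after delivery.
- Post-discharge days covered = max(0, 7 − L).
- Days lost = min(7, L); share lost = min(7, L) / 7.

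| Assumed L (days) | Days covered | Share covered | Share lost |
|---|---|---|---|
| 0 | 7 of 7 | 100% | 0% |
| 1 | 6 of 7 | 86% | 1/7 = 14% |
| 2 | 5 of 7 | 71% | 2/7 = 29% |
| 3 | 4 of 7 | 57% | 3/7 = 43% |
| 5 | 2 of 7 | 29% | 5/7 = 71% |
| 7 or more | 0 of 7 | 0% | 100% |

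**One case.** Among caesareans, the data extraction component excludes only elective ones, so a woman who has an intrapartum caesarean stays in. Suppose she goes home on day 4 and returns with a complication on day 9. The return is 9 − 4 = 5 days after discharge, so it meets the outcome definition. Day 9 is later than day 7, so it lies outside the collection period.

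**Between arms.** If L were 2 days in one arm and 3 in the other, the first would be covered for 5 days and the second for 4. The arm with the shorter stay has more time in which a return can be counted. This is only an illustration; the article says nothing about stay by arm.

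**After the fix.** If collection for this item runs to day L + 7, all 7 days are covered for every L.

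**Does it reach the primary outcome?** The composite's components are not defined from discharge. The sample size reproduces from its own inputs: 15% against 7.5%, two-sided 5%, 80% power gives 278 per arm. The design effect is 1 + 299 × 0.01 = 3.99, and 278 × 3.99 = 1109. Then 1109 / 300 = 3.7, rounded up to 4 clusters, or 1200 per arm. Allowing for non-response, 1200 / 0.95 = 1264 per arm, or 2528 in total against the stated 2530. None of this depends on the return window.

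**The case against.** **The outcome wording is loose.** It could mean a return that follows discharge and falls in the first 7 days of life, which would match the collection period. This is the less natural reading. It would remove the textual conflict, but each pair could still have a counted return on only 7 − L days, so comparability would still depend on stay.

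**The article does not say how a later return would be coded.** This stands. A data collector manual and standardised case definitions are planned and not shown. A reader might infer that a day-9 return will be entered as no return; the article says only that the reviewed period ends before it. The mismatch between two stated rules remains.

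**The bias has not been shown.** This also stands. A reader might infer that the sickest pairs lose most of the window and are the likeliest to return, or that the comparison between arms is biased. The arithmetic supports only that a longer postnatal stay means a shorter observed window. The article gives no length of stay, return rate or timing of returns by severity, and no expected effect on stay.

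**The outcome is minor.** It appears in one sentence. It is not in the objectives, the abstract, the two outcomes described in the Secondary outcomes section, or the sample size. That limits the importance of the point but does not make the two windows consistent.

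**Extending all extraction could do harm.** This is correct and shapes the fix. The same extraction feeds the primary composite. Searching every record to 7 days after discharge would mean that pairs with longer stays are searched longer for primary events.

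**Conclusion.** The point holds as a conflict between two stated windows, confined to one secondary outcome. As written, the plan covers max(0, 7 − L) of the 7 post-discharge days: full coverage only for same-day discharge, and none from L = 7 onwards. The conclusion assumes the natural reading of the outcome and collection that stops where the Data extraction section says it does. The values of L are assumptions.

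The percentages are shares of window days. A reader might take them as shares of returns missed, but that would need the timing of returns, which the article does not give. Undercounting follows for any return in the uncovered days. Unequal observation between arms is possible if the intervention changes stay, with size and direction unknown. The change should be made, but nothing in the primary analysis depends on it.

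**What to change.** In the Data extraction section, record the discharge date for each pair. For the return-after-discharge item only, continue extraction to 7 days after discharge, including for the last pairs recruited. Keep the existing limit of 7 days after delivery for the components of the primary composite, so that their ascertainment does not come to depend on stay.

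Redefining the outcome from delivery would also reconcile the text, but would leave time at risk dependent on stay.

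The cost is a sentence in the protocol and the manual, and one date field. The return item closes L days later for each pair, and the end of extraction moves by about a week. The coaches already review records twice a week. The sources named in the article are birth registries, charts, the partograph, the temperature sheet and mothers' health books, so the team should confirm that these record returns. At this protocol version recruitment had not begun, and the article provides a route for amendments.

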### Statistical methods

The analysis will be per intention to treat. Descriptive statistics for the study sample will be computed using means and standard deviations or medians and interquartile ranges (IQR) for continuous covariates, and proportions will be used to describe categorical variables. We will make use of the Rao-Scott chi-square test statistic, which adjusts for the matched-pair, cluster randomization scheme [24], to compare the rates of the primary and secondary outcomes in the comparison and intervention groups if the randomization scheme was found effective. Possible multivariable modeling techniques to correct for potential imbalances between study groups include Generalized estimating equations, multilevel Poisson modeling and multilevel cox models. The data analysis will be carried out using Stata 15.1 software. A *p*-value< 0.05 will be necessary to consider intervention and comparison groups significantly different.

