#### Secondary outcomes

The first secondary outcome is the level of adherence to EBPs by healthcare providers during childbirth and early postpartum. This will be measured as a rate of successful delivery of key EBPs included in the modified WHO-SCC at each birth event. The provision of key EBPs will be ascertained in a sample of birth events using direct observation with possible cross-validations with data from birth registries and mothers’ health books when necessary. The anticipated best practices to be assessed in this study include: the assessment for need of reference, the use of a partograph, assessment for history and actual bleeding, vision blurred, HIV status, correct use of magnesium sulfate, uterotonics and antibiotics, early initiation of breastfeeding and skin-to-skin contact, and discussions around family planning services.

The second secondary outcome is the rate of availability of essential safe childbirth supplies measured at health facility level. A facility assessment questionnaire will be used to collect data on the availability of essential safe childbirth supplies as baseline assessment prior to the onset of the study. Six months after the launch of the study an end line survey will be conducted using the same questionnaire.

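### The primary analysis is chosen by observed balance, so its type I error is not controlled at 5%; one analysis should be named in advance

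*Protocol article*

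**What the plan says.** The protocol article, under Statistical methods, names the Rao-Scott chi-square test for the primary and secondary outcomes and says that it accounts for the pairs and clusters. It is to be used for comparing rates "in the comparison and intervention groups if the randomization scheme was found effective". The next sentence reads: "Possible multivariable modeling techniques to correct for potential imbalances between study groups include Generalized estimating equations, multilevel Poisson modeling and multilevel cox models". A single criterion closes the paragraph: a p-value below 0.05 "will be necessary to consider intervention and comparison groups significantly different".

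The article does not say how or when effectiveness of the randomisation is judged, on which variables, or which model takes over. No other section names one primary analysis.

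The sample size for the primary outcome rests on one test: "With a bilateral type I error set at 5" per cent, and "for a statistical power of 80%, assuming an intra-class correlation coefficient of 0.01".

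For the supplies outcome, the Secondary outcomes section plans a survey before the start and a second one: "Six months after the launch of the study an end line survey will be conducted using the same questionnaire".

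**The concern.** The condition treats balance as a test of whether randomisation succeeded. In a properly conducted randomisation, imbalance arises by chance, so observed balance cannot answer that question. It only decides which p-value becomes the main one.

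The candidate analyses are not interchangeable. The Rao-Scott test is unadjusted for covariates. A Poisson model gives a rate ratio and a Cox model a hazard ratio. GEE is an estimation method whose effect measure depends on the link chosen. The composite is recorded as present or absent for each birth, so no event time is defined from which a hazard could be estimated.

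Under Data extraction, socio-demographic and outcome data are collected together. Balance on the women's characteristics would therefore be read from the same data set that holds the outcomes, and the text does not require an earlier or blinded decision.

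At stake is whether a reader of the results can tell which p-value was primary. This matters because the Dissemination plans section links national scale-up to the findings.

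**Working it through.** **1. The plan's own figure.** The inputs are a control rate of 15% ("at least one of the component outcomes would be observed in an average 15% of vaginal deliveries"), "a half reduction in the incidence of the primary outcome for the intervention group" (so 7.5%), two-sided 5%, 80% power, ICC 0.01 and a cluster size of 300.

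- Two proportions, no continuity correction: n = [1.96·√(2·0.1125·0.8875) + 0.842·√(0.15·0.85 + 0.075·0.925)]² / 0.075² = 278 per arm. With continuity correction: 304.
- Design effect: 1 + 299 × 0.01 = 3.99.
- 304 × 3.99 = 1213 (278 × 3.99 = 1109). The stated 1200 is within about 1% of the corrected figure, and without the correction 1200 gives about 83% power.
- 2 × 1200 / 0.95 = 2527, against 2530 stated.

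The figure reproduces, and it presupposes one test at two-sided 5%.

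**2. How often imbalance would appear.** For a facility-level covariate with SD 1 and K hospitals per arm, ignoring the matching, the difference in means has SD √(2/K).

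- K = 4: SD = 0.707, and P(|difference| > 0.5) = 2·[1 − Φ(0.707)] = 48%.
- K = 12: SD = 0.408, and the probability is 22%.

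**3. Type I error.** The simulation had 40,000 null trials per scenario, 4 v 4 clusters of 300 births, a 15% event rate, ICC 0.01 and one facility-level covariate. Its correlation r with the cluster rate is assumed. Cluster-level tests with a t reference stand in for the named methods, and the matching is not used in the switching rules. The Monte Carlo standard error is about 0.1 percentage point.

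| Rule | r = 0 | r = 0.5 | r = 0.8 |
|---|---|---|---|
| One fixed test, no covariate | 4.8% | 4.9% | 5.0% |
| One fixed test, adjusted | 4.9% | 4.9% | 4.9% |
| One fixed paired t test | 4.9% | 4.9% | 4.9% |
| Switch to adjusted if balance test p < 0.05 | 4.8% | 4.6% | 3.9% |
| Switch to adjusted if difference > 0.5 SD | 4.9% | 4.3% | 3.3% |
| Smaller of the two p-values | 6.6% | 7.3% | 8.2% |

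A second simulation on eight facility means, with balance judged at p < 0.05 or p < 0.20 and r of 0.5 to 0.8, gave 2.3–4.5% for the switch, 7.5–8.7% for the better of the two analyses, and 5.0% for always adjusting. With 12 pairs and r from 0 to 0.8, the first simulation gave 2.9–4.8% for the switch and 5.7–8.2% for the smaller p-value.

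The mechanical switch is conservative for a prognostic covariate because the unadjusted test is kept only when the covariate happens to be balanced. The difference in outcomes then varies less than its standard error assumes.

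**4. Precision of facility-level adjustment.** The expected variance relative to no adjustment is (1 − r²) × [1 + 1/(f − 2)], where f is the degrees of freedom for the covariate's residual variation.

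- 8 unpaired hospitals, f = 6, factor 1.25: r = 0.5 gives 0.94 (6% lower); r = 0.8 gives 0.45 (55% lower).
- 4 pairs, pairing kept, f = 3, factor 2: r = 0.5 gives 1.50 (50% higher); r = 0.8 gives 0.72 (28% lower). Break-even is at r = √0.5 = 0.71.
- 12 pairs, f = 11, factor 10/9: r = 0.5 gives 0.83 (17% lower); r = 0.8 gives 0.40 (60% lower); r = 0 gives 1.11 (11% higher).

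In the paired cases r is the correlation of within-pair differences. The last line also applies to endline supplies adjusted for the same hospital's baseline and for pair.

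**The case against.** The strongest reply is that the stated rule, applied literally, does not inflate the error. A switch driven only by baseline imbalance rejects at or below 5%, and the 7–9% belongs to a different practice, reporting the better result, which the article does not propose. This stands. A reader might infer that the plan has an inflated false-positive rate, and the documents do not support that. They support only that the rate is not controlled, because no criterion, covariate list or order of models makes the switch mechanical.

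A reader might also infer that the choice will be made with outcomes in view. The article gives no timing, and the matching variables are known before launch, so this is possible but not stated.

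A third reply is that a SAP may settle the matter. But the condition is written into the protocol, so a SAP naming one unconditional analysis would have to contradict it. Reading the models as supplements to the test does not help either, since the test itself remains conditional.

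Two further limits stand. The simulations do not use the matching, so they illustrate the mechanism and do not reproduce the trial's analysis. And Cox models need not be ruled out for every outcome: return within 7 days could be analysed as time to event.

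On supplies, the article does not say that the baseline survey will be left out of the analysis, so that part is a suggestion, not an error.

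**Conclusion.** The point holds in this form: the main comparison depends on observed balance, by a criterion that is not given and with an open set of alternatives, so its type I error is not controlled at the 5% that the sample size assumes. For one facility-level covariate with an assumed correlation of 0.5 to 0.8, the plausible range runs from about 2–5% (mechanical switch) to about 7–9% (discretionary choice between two analyses). The direction cannot be read from the document. One fixed analysis with a small-sample reference distribution gives about 5%.

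A reader might infer that precision is also being lost. That is not supported for a single country: with four pairs, facility-level adjustment changes the variance by anything from +50% to −28% over the same range of correlations. For supplies pooled over all 12 pairs, a cut of about 17–60% is available if the baseline–endline correlation is 0.5 to 0.8 (assumed), with a loss of about 11% if it is near zero.

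**What to change.** Delete the clause that makes the Rao-Scott test conditional. Name one primary analysis that respects the matched pairs, has a small-sample reference distribution, and is used whatever balance is observed. It should have either no covariates or a short fixed set confirmed as collected, for example maternal socio-demographic items on the extraction form. State its effect measure. Report the other models as sensitivity analyses, and do not use a Cox model for the present/absent composite.

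As an optional addition, analyse endline supply availability per hospital, adjusted for that hospital's baseline survey and for pair, pooled over the 12 pairs if the team accepts pooling across countries for this outcome.

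The cost is wording, with no new data. It should be settled before outcome data are examined. The article already provides for changes to the statistical analyses to be documented, published as amendments and entered in the registry.
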